#### Allocation concealment

2.3.2

Allocation concealment will be maintained through a centralized randomization process. The randomization lists will be kept securely by the independent researcher who will have no role in participant recruitment, enrollment, intervention delivery, or outcome evaluation, or data analysis.

After completion of the baseline assessment and confirmation of the participant’s disability risk level, the enrolling investigator will contact the independent researcher and provide the relevant risk-stratification information. The independent researcher will then assign the participant to the intervention or control group based on the corresponding pre-generated randomization list for that risk stratum. Members of the research team responsible for recruitment, baseline assessment, intervention delivery, and outcome evaluation will not have access to the randomization sequences before group assignment. This procedure is intended to preserve allocation concealment and reduce the risk of selection bias.

#### Blinding

2.3.3

Given that the intervention is delivered through a digital platform, blinding of participants and intervention providers is impractical. The intervention component of the trial will therefore be conducted as an open-label procedure. However, blinding will be applied to outcome assessment and data analysis. Specifically, outcome assessors and statisticians will be unaware of participants’ group assignments until the primary analyses have been completed.

To reduce the possibility of unblinding, separate staff members will be assigned to intervention-related tasks and outcome evaluations. Outcome assessors will not be involved in intervention delivery, follow-up management, or access to the digital platform usage records. Group allocation information will not be included in outcome assessment forms or in the datasets provided to outcome assessors. Participants will be reminded at each assessment visit not to discuss or disclose their allocation status or intervention experience to the assessors. If accidental unblinding occurs, it will be documented, and another blinded assessor will complete the assessment or subsequent assessments where feasible. Data analysis will be performed using coded group labels until the primary analyses have been completed.

### Interventions

2.4

#### Intervention group

2.4.1

Participants in the intervention group will receive a digital platform-based stratified intervention program designed for disability risk prevention.

In this study, the Disability Risk Prevention Management Platform for Older Adults (DRPP) was developed by the Second Affiliated Hospital, Zhejiang University School of Medicine. It was constructed to provide community-dwelling older adults with integrated services for disability risk assessment, ongoing monitoring, and personalized intervention delivery.

The intervention model embedded in the platform was developed based on risk-stratified management and comprehensive geriatric care. Evidence-based recommendations were organized into four intervention domains, namely physical activity, nutrition, rest and sleep, and psychological and social support. Across these domains, 87 intervention components were identified and incorporated into the system as a structured knowledge base. These components were then converted into digital materials suitable for platform-based delivery.

The platform provides different intervention packages according to the participant’s level of disability risk. Among low-risk participants, the intervention focuses primarily on maintaining functional ability and promoting healthy behaviors, including regular exercise, adequate nutrition, good sleep practices, and engagement in social activities. For participants classified as moderate risk, the intervention places greater emphasis on structured exercise delivered at a higher frequency. Participants in the high-risk group receive a more intensive and continuous intervention package, with careful attention to safety throughout the process. In addition to disability risk level, intervention components were further adapted according to clinical and functional tailoring factors, including SPPB, frailty status, balance capacity, BMI, depression status, sleep and specific chronic conditions such as hypertension. The stratified intervention strategies are shown in Table 2. The measures of the tailoring factors are shown in Supplementary Table 1. The details of intervention contents are provided in Supplementary Table 2.

**Table 2 tab2:** Stratified intervention strategies for disability prevention in older adults.

Tailoring factors	Intervention component	Format (selectable based on individual preference)	Recommended dose / check-in frequency		
			High risk	Moderate risk	Low risk
/	Warm-up exercise	Marching in place / Joint mobility exercise / Dynamic stretching	10 min/session; accompanying exercise training		
SPPB ≥ 10	Aerobic exercise	Jogging / Stair climbing / Aerobic dance	20 min/session; 2 times/week	20 min/session; 2 times/week	20 min/session; 1 time/week
/		Brisk walking / Swimming / Baduanjin	30 min/session; 4 times/week	30 min/session; 3 times/week	30 min/session; 2 times/week
SPPB ≤ 9 or frailty		Walking / Housework / Tai Chi	50 min/session; 3 times/week	40 min/session; 3 times/week	40 min/session; 2 times/week
Frailty or upper limb muscle strength grade 3–4	Resistance exercise	Bodyweight exercises - chest expansion / straight arm abduction	10 reps/set, 3 sets/day; daily	10 reps/set, 2 sets/day; daily	10 reps/set, 2 sets/session; 3 times/week
		Bodyweight exercises - half-squat stand / heel raise / seated leg extension	10 reps/set, 3 sets/day; daily	10 reps/set, 2 sets/day; daily	10 reps/set, 2 sets/session; 3 times/week
Balance capacity grade ≤ 3; or history of falls / Parkinson’s disease / stroke	Balance exercise	Static balance exercise/ Dynamic balance exercise	15 min/session; 2 times/week	10 min/session; 2 times/week	10 min/session; 2 times/week
/	Cool-down exercises	Marching in place / Joint mobility exercise / Dynamic stretching	10 min/session; accompanying exercise training		
/	Dietary pattern^*^	Mediterranean diet	3 times/week	2 times/week	1 time/week
Frailty or muscle strength ≤ grade 3		High-protein diet	3 times/week	2 times/week	1 time/week
History of hypertension		DASH diet	3 times/week	2 times/week	1 time/week
BMI ≤ 18.5 (age <70) or BMI ≤ 20 (age ≥70)		High-calorie diet	3 times/week	2 times/week	1 time/week
History of diabetes		Low-glycemic diet	3 times/week	2 times/week	1 time/week
History of digestive disease		Age-friendly diet	3 times/week	2 times/week	1 time/week
Frailty or muscle strength ≤ grade 3	Nutrient supplement ^*^	Protein(1.2 g/kg/d)	3 times/week	2 times/week	1 time/week
Female: age ≥65; Male: age >70		Calcium(1,300 mg/d)	3 times/week	2 times/week	1 time/week
Male: 65 < age≤70		Calcium(1,000 mg/d)	3 times/week	2 times/week	1 time/week
Age ≥ 65		Vitamin D(800 U)	3 times/week	2 times/week	1 time/week
/	Sleep guidance	Healthy sleep education	1 time/week		
PSQI ≥ 7	Relaxation and meditation	Relaxation and meditation training	15 min/session; 1 time/week		
MMSE ≤ 20 (primary school or below) or MMSE ≤ 24 (middle school or above) or self-rated memory fair or poor	Memory training	Episodic memory / working memory / associative memory training	20 min/session; 3 times/week	15 min/session; 3 times/week	15 min/session; 2 times/week
MMSE ≤ 20 (primary school or below) or MMSE ≤ 24 (middle school or above)	Attention training	Dual-task walking/ deep breathing exercise	20 min/session; 3 times/week	10 min/session; 3 times/week	10 min/session; 2 times/week
/	Executive function training	Object sorting task / grocery shopping or purchasing vegetables	30 min/session; 2 times/week		
No participation in any social activities in the past month (including chatting with neighbors, playing cards, volunteering, etc.)	Psychosocial support	Participate in community activities / volunteer activities/ family visits	1 time/day		

In the tailoring factor column, a slash (/) indicates that the intervention component is delivered by default (i.e., without any additional condition) to all participants at the corresponding risk level. Other entries (e.g., SPPB≥10, frailty) indicate conditionally delivered components—they are automatically recommended or pushed to a participant only if the corresponding clinical or functional factors met, based on baseline or dynamically reassessed data. SPPB, Short Physical Performance Battery; BMI, body mass index; DASH, Dietary Approaches to Stop Hypertension; MMSE, Mini-Mental State Examination; PSQI, Pittsburgh Sleep Quality Index. *The recommended frequency refers only to the number of check-ins required per week for a fixed dietary pattern or nutrient supplementation task. However, dietary pattern and nutrient supplementation should be maintained daily.

To improve acceptability and usability of the intervention among older adults, digital materials were redesigned in age-friendly formats. To enhance compliance and ensure correct performance, a series of illustrated demonstration videos were formulated by rehabilitation professionals, along with simple verbal instructions. Cognitive and psychological content was delivered with animated videos. The use of large letters and graphical illustrations helped in better readability of nutrition and social support material.

Once the risk assessment of the disability of a participant is done, the platform implements a pre-defined stratified algorithm for the creation of an individualized intervention plan. The plan can also be changed based on the participant’s preferences. All the plans offer a set of intervention tasks across the four domains along with recommendations on how often to train, at what intensity, what to eat, safety and follow-up reminders. Throughout the intervention period, the platform will continuously collect information on user engagement, including task completion, check-in records, and follow-up responses. The data will help in monitoring the adherence, making the required alteration of the intervention plan in a timely manner, and improving the precision of subsequent recommendations.

The entire duration of the intervention will be 6 months long. During the intervention, participants will undergo periodic reassessment of disability risk related factors and risk level, and the intervention plan will be adjusted accordingly. The frequency of reassessment and plan adjustment will depend on the participant’s current risk level: every 3 months for low-risk participants, every 2 months for moderate-risk participants, and once per month for high-risk participants. If a participant’s risk level changes, the participant may move to another intervention risk tier, and the intervention packages will be modified according to the updated risk level. This dynamic adjustment will be used only to tailor the intervention during follow-up and will not alter the original randomization allocation.

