#### Sample size calculation

2.2.5

The sample size calculation was based on the expected difference in Short Physical Performance Battery (SPPB) scores between the intervention and control groups. In a published study of community-dwelling older adults in China, the average baseline SPPB score of 1,014 older adults was (8.92 ± 2.11) (28). For the expected between-group difference, a 1-point difference in SPPB was selected as the target clinically meaningful effect based on previous evidence that most estimates of substantial change for the SPPB ranged from 0.99 to 1.34 points (29). On this basis, the mean SPPB score was assumed to be 8.92 in the control group and 9.92 in the intervention group. Using PASS software, and assuming a two-sided *α* of 0.05 together with a power of 90%, the required number of participants was estimated to be 95 per group, corresponding to 190 participants in total. Considering a potential dropout rate of 20%, the sample size was adjusted to 238 participants.

Preliminary data further suggested that the proportions of older adults at high, moderate, and low risk of disability were approximately 1:5:4. Based on this distribution, the final sample is expected to comprise about 24 high-risk participants, 120 moderate-risk participants, and 94 low-risk participants.

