Analyses of secondary outcomes will be selected according to the type and distribution of each variable. Continuous outcomes will be analyzed using mixed-effects models or repeated-measures methods, as appropriate. For categorical outcomes, including the occurrence of disability, between-group comparisons will be conducted using chi-square tests, and logistic regression models may be used to estimate odds ratios with corresponding 95% confidence intervals. Potential confounders or clinically relevant baseline variables may be included in multivariable models when adjustment is warranted. Urban/rural residence will be considered in the adjusted analyses where appropriate. Subgroup or sensitivity analyses by urban/rural residence will be conducted, if sample size permits, to explore whether intervention effects differ between urban and rural participants.

Missing data will be handled using multiple imputation or likelihood-based methods under the missing-at-random assumption. All analyses will be conducted using R version 4.0.3 and SPSS version 29.0 (IBM Corp., Armonk, NY, USA). Statistical tests will be two-sided, with statistical significance defined as *p* < 0.05.

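### Risk tier decides which package a participant receives and is the randomisation stratum, yet the SPPB analysis has no risk-tier term and the only subgroup factor named is urban/rural residence

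*Protocol article*

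**What the plan says.** Section 2.2.5 expects "about 24 high-risk participants, 120 moderate-risk participants, and 94 low-risk participants", so no risk level dominates and low risk makes up about two-fifths of the sample. The same section sizes the trial on a single contrast for everyone: "a 1-point difference in SPPB was selected as the target clinically meaningful effect", and "the mean SPPB score was assumed to be 8.92 in the control group and 9.92 in the intervention group".

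Sections 2.1.2 to 2.3.1 should be read with 2.4.1. Randomisation is 1:1 within each disability-risk stratum (2.3.1), and the platform then selects the package by risk level (2.4.1). On the low tier the text reads: "Among low-risk participants, the intervention focuses primarily on maintaining functional ability and promoting healthy behaviors". The sentence goes on to list exercise, nutrition, sleep and social activity. In Table 2 many components are lighter in the low tier. The default brisk-walking row, for example, is 2, 3 and 4 times a week from low to high risk. Other components are the same across tiers.

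Section 2.7 gives the SPPB model as a linear mixed model with group, time point, group-by-time and a person-level random effect. On subgroups it says: "Subgroup or sensitivity analyses by urban/rural residence will be conducted, if sample size permits". It also allows clinically relevant baseline variables as adjusters, and adds a conditional sensitivity analysis that leaves out participants with high baseline SPPB. Risk tier appears in none of these by name.

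**The concern.** The trial evaluates a programme whose defining feature, according to its own Discussion, is that intensity follows predicted risk. The single pooled SPPB contrast averages over three packages with different emphases. If the pooled result is close to null, the plan as written cannot separate no effect anywhere from an effect confined to the higher tiers. If it is positive, the plan cannot say whether low-risk participants, about 40% of those treated, contributed to it. A tier analysis added after unblinding would be post hoc, although the tier is known before randomisation.

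The article does not leave subgroups wholly to another document. It names one factor, and that factor is not the one on which the intervention is built.

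**Working it through.** **Inputs (2.2.5 unless noted).** Difference 1 point; SD 2.11; two-sided alpha 0.05; power 90%; dropout 20%; expected tiers 24 high, 120 moderate, 94 low; 1:1 allocation within tier (2.3.1).

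**Step 1: the plan's own figure.**
- Normal approximation: n = 2 × (1.96 + 1.2816)² × 2.11² / 1² = 93.6, so 94 per group.
- Two-sample t-test (noncentral t): 95 per group, power 0.901, total 190.
- Dropout: 190 / 0.8 = 237.5, so 238.

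The stated 95, 190 and 238 reproduce.

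**Step 2: the mix.** Low risk 94/238 = 39.5%. Moderate plus high 144/238 = 60.5%.

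**Step 3: how much the pooled effect could depend on the low tier (illustration).** The documents give no tier-specific effects. Assume 1 point in moderate plus high risk and a varying effect d in low risk:

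pooled = 0.605 × 1 + 0.395 × d

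Power is for a single-time-point t-test with 95 per group and SD 2.11.

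| Assumed low-tier effect d | Pooled effect | Power |
|---|---|---|
| 0 | 0.61 | 50% |
| 0.25 | 0.70 | 63% |
| 0.5 | 0.80 | 74% |
| 0.75 | 0.90 | 83% |
| 1.0 | 1.00 | 90% |

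The planned analysis is a repeated-measures model, so these powers are approximate. For a change-score comparison, the variance is 2 × SD² × (1 − r), where r is the within-person correlation, which the documents do not give. At r = 0.5 the table is unchanged. At r = 0.7, power is about 72% for a pooled effect of 0.61 and 92% for 0.80. Below r = 0.5 it is lower than shown.

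**Step 4: what a tier analysis could deliver.** Half-width = 1.96 × 2.11 × √(2/m), with m completers per arm after 20% dropout.
- Low: m = 94 × 0.8 / 2 = 37.6, half-width 0.95.
- Moderate plus high: m = 144 × 0.8 / 2 = 57.6, half-width 0.77.
- High alone: m = 24 × 0.8 / 2 = 9.6, half-width 1.89, too wide to be useful. This is why the two upper tiers are combined.

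Interaction (low versus moderate plus high), true difference 1 point:
- All randomised: SE = 2.11 × √(4/94 + 4/144) = 0.560; power = Φ(1/0.560 − 1.96) ≈ 43%.
- After dropout: SE = 0.560 / √0.8 = 0.626; power = Φ(1/0.626 − 1.96) ≈ 36%.

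**The case against.** The strongest reply is that nothing here is wrong as stated. The second aim asks whether the stratified programme works, and the pooled intention-to-treat contrast answers that. A full analysis plan, not shown, may list more subgroups. Section 2.7 does not say that urban/rural is the only one. Tier at baseline also does not fix the package throughout: section 2.4.1 reassesses risk every 1 to 3 months and lets participants change tier, and it tailors further by SPPB, frailty and other factors. Finally, the tier analysis would be imprecise.

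Most of this stands, and it limits the point to an exploratory addition. It does not remove it. Section 2.7 does take up subgroups and passes over the randomisation stratum. Baseline tier is the one version of risk level that randomisation protects, whatever happens to tier later. The conditional high-SPPB sensitivity analysis is related but is not defined by tier.

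A reader might go further and infer that the 1-point target is diluted and the true power is well under 90%. The documents do not support that:
- The low-tier effects in Step 3 are assumptions, and the low-tier package includes regular exercise.
- The endpoint is a between-group difference. Maintaining function produces one if controls decline, and the stated aim is to delay decline. The planning mean of 8.92 for controls equals the cited baseline mean, but section 2.2.5 does not say that controls will stay level.
- The 1 point is chosen as a clinically meaningful target, not forecast as the average response.

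A reader might also compare the effect the upper tiers would need if the low tier gained nothing (1 / 0.605 = 1.65 points) with the cited 0.99 to 1.34. That range describes estimates of what counts as substantial change. It does not cap the achievable effect, so exceeding it does not show implausibility.

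**Conclusion.** The point holds as a gap in the planned analysis, not as an error in the sample size. About 40% of participants are expected in a tier with a maintenance-focused package, and tier governs both randomisation and the package. The SPPB analysis as written nevertheless contains no tier term and pre-specifies no tier estimate. The pooled contrast remains valid and should remain primary.

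How much this matters depends on tier effects that the documents do not give. With assumed low-tier effects of 0 to 0.5 point, the pooled effect would be 0.61 to 0.80 and single-time-point power about 50% to 74%. With an equal effect in all tiers, nothing is lost. These figures show why the tier estimates are worth having; they do not show that the stated 90% is wrong. The tier results can inform interpretation only, because interaction power is about 36% to 43% under SD 2.11.

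**What to change.** In section 2.7:
- Include baseline (randomised) risk tier in the SPPB mixed model.
- Pre-specify an exploratory group-by-time-by-tier interaction, with its lower-order terms. Report 6-month between-group estimates and 95% CIs for low risk and for moderate plus high risk combined.
- Define tier as assigned at randomisation, regardless of later movement between tiers.
- Name this analysis ahead of the urban/rural subgroup, and state that the pooled intention-to-treat contrast remains primary.

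Section 2.2.5 can stay as it is. Its figures are right for the chosen target, and there are no documented tier effects from which to build a weighted one.

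The cost is a sentence or two of text, with no extra participants or data, since tier is recorded before allocation. The drawback is imprecision, as shown in Step 4 of the working. The text should therefore say that no confirmatory claim will be made for any tier, and that a non-significant interaction will not be read as evidence of equal effects.

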#### Control group

2.4.2

Participants of the control group will be provided with the regular community-based geriatric health management services delivered by community health centers. These services are provided according to the National Basic Public Health Service Program and the Zhejiang Provincial Basic Public Service Standards (2021 version) and therefore represent the standard care routinely available to older adults in the participating communities.

Standard care generally includes routine health education and basic lifestyle counseling provided by general practitioners and community health workers. The content may cover healthy aging, chronic disease prevention and control, smoking cessation, physical activity, nutrition, and basic dietary and exercise advice. The frequency, content, and format of standard care will follow these established routine procedures rather than being determined by the study team. However, no additional study-specific intervention, structured risk-stratified management, individualized monitoring, or extra follow-up beyond routine community practice will be arranged for the control group.

And participants in the control group will not have access to the digital platform, risk-stratified intervention protocols, individualized monitoring, or structured feedback mechanisms provided to the intervention group. For ethical reasons, participants in the control group will be offered access to the digital platform after the study period has been completed.

### Measures

2.5

#### Disability risk factors assessment

2.5.1

Based on the disability risk prediction model developed by the research team, a total of 29 factors will be assessed across six domains: sociodemographic characteristics, lifestyle factors, family and economic support, comorbidities and hospitalization, health status and functional limitations, and physical examinations. Sociodemographic characteristics include age, gender, education level, retirement status, and history of accidents or falls. Lifestyle factors include smoking status and participation in social activities. Family and economic support includes financial support. Comorbidities and hospitalization include history of 7 specific chronic conditions, namely hypertension, diabetes, chronic lung diseases, psychiatric illnesses, heart disease, digestive diseases, and arthritis, as well as hospitalization last year. Health status and functional limitations include self-reported physical limitations, including difficulty in extending arms, lifting weights, picking up a small coin, climbing stairs, walking for 100 meters, standing up from chair, and stooping, as well as self-reported orientation and depression. Physical examinations include Body Mass Index (BMI), waist circumference, side-by-side stand test and tandem test. Detailed assessment procedures and definitions are provided in Supplementary Table 3.

